### **3.5. Entomology**

#### **3.5.1. Objectives of the entomological monitoring:**

The main objectives of entomological monitoring are;

- a. To determine abundance and relative proportion of *Anopheles gambiae* and *An. funestus* sibling species between study arms
- b. To record differences in EIR between study arms

Secondary objectives

- c. To monitor resistance in vector and nuisance biting mosquitoes.
- d. To assess insecticide longevity
- e. To assess behavioural change

#### **3.5.2. Main entomological activity**

Monitoring of mosquito population density, human biting rates, entomological inoculation rate  
 Mosquito control through IRS has been ongoing in Muleba since 2007 and is likely to have had a significant impact on mosquito populations. Pre-IRS surveys by NIMR Mwanza showed the presence of both *An. funestus* and *An. gambiae s.l.* The relative composition and abundance of these species is likely to have changed significantly as a result of IRS.

##### **Pilot: stage 2**

During stage 2 (pilot) the purpose of mosquito trapping is to guide our subsequent entomology protocol during stage 3 (baseline) and stage 4 (intervention years). 200 trap nights and space spray catches in 200 additional houses will be conducted during the pilot to determine the abundance and relative proportion of vector species. The 8 houses will be selected at random in the core sampling area of each cluster. For each of the selected houses a description of the HH will be done using a questionnaire, including information on the number of inhabitants, type of house (wall, roof, number of rooms, number of sleeping places etc.), presence of animals and malaria prevention measure (IRS, net, any others) used by the household members.

Reports from the district indicate a substantial decrease in malaria following IRS and this may have resulted in very low mosquito densities. If mosquito catches are prohibitively low during the pilot survey, longitudinal monitoring during the baseline and intervention period may lack sufficient power. This information will allow us to modify the entomology protocol to be more intensive during certain time periods for specific objectives such as resistance monitoring and

sporozoite infectivity. Relative proportions of *An. funestus* and *An. gambiae s.l.* trapped during the pilot determine which probes are to be ordered for species identification.

#### Entomological monitoring during stage 3 and 4

Fifteen clusters per study arm will be selected for longitudinal entomological monitoring. Collections are done monthly during one day/night in 10 households in each of the clusters. Collection is done by using the best method, light traps or space spray catches, depending on the result of the pilot. The methods will be similar to those used in the pilot including household questionnaires etc.

This gives an estimate of the number of mosquitoes and any change in the size of the mosquito population in the village due to the IRS and LLIN interventions. Each cluster is trapped once a month. The catches are identified to species, counted and feeding status recorded. Females are stored in individual capsule and kept for sporozoite analysis, for sibling species identification, and kdr testing, males are discarded.

### 3.5.3. Additional entomological activities

#### Behavioural change assessment

As vector control activities have been ongoing for several years there is a possibility that indoor resting and biting mosquitoes may have been selected for behavioural modification and outdoor resting/biting may be more common. Sentinel cows and pit trap collections will be used for periodic sampling for evidence of outdoor biting. By using a variety of trapping methods we are able to show changes in distribution, density and behaviour of a range of mosquito vector species that exhibit different behaviour and observe any changes in resting preference over time in response to different IRS frequency and increase in LLINs.

#### Insecticide residual activity on sprayed walls and LLINs and insecticide resistance

It is important for us to monitor coverage and quality of IRS and LLINs during the intervention year. Pyrethroid detection kits for IRS and LLINs developed by LSHTM will be deployed to verify spray coverage and continuing efficacy of LLINs.

Cone bioassays will be carried out bi-monthly post spraying during the stage IV to determine residual activity of the IRS insecticide. Where possible we shall work in partnership with the entomology unit of NIMR Mwanza, which has been monitoring insecticide performance for RTI, for bioassay of IRS surfaces.

#### Insecticide resistance in vector and nuisance-biting mosquitoes

Pyrethroid resistance is a particular concern in areas of high selection pressure where pyrethroid IRS and pyrethroid LLINs are used. WHO resistance tests will be carried out once a year using pyrethroid test papers in WHO kits. Percentage mortality, median time to knockdown, and LD50s response to pyrethroids will be measured. Longitudinal sampling of mosquitoes and testing for kdr and other resistance markers will allow detection of resistance and selection in the two study arms.

### 3.5.4. Laboratory analysis

There are several laboratory techniques that will be important in producing robust entomological outcomes.

Entomology techniques planned for this study include mosquito sibling species identification (*An. gambiae* & *An. funestus* complexes) and investigation of resistance mechanisms (Kdr) through real-time multiplex PCR, sporozoite ELISA and blood-meal identification.

Some of the protocols involving conventional low-throughput systems have been updated for high throughput and cost-effective analysis of samples following the IVCC Vector Population Monitoring Tool.

To fulfil the objectives set out in the workplan initial training will be required, the Liverpool School of Tropical Medicine (LSTM) have agreed to be involved in equipment set-up and protocol training.

### **3.6. Interventions**

During stage 2 in February 2011 an IRS round has been completed in Muleba district including all the selected clusters of our survey area. Another round is planned in September-October 2011 and will target only half of the cluster randomly selected to the IRS plus LLINs study arm.

In March 2011, a LLIN distribution campaign supported by Mennonite Economic Development Associates (MEDA) and funded by Global Fund is scheduled and aims to reach universal coverage. However preliminary information shows a really low bed-net usage, this suggests that an intensive Information Education Communication (IEC) campaign is required to get high usage of LLINs.

Additional net will probably need to be secured to top up the universal coverage campaign and insure that every sleeping place is covered by a LLIN in the survey area. The bed-net coverage given by the pilot survey will help us to estimate the quantity of LLINs needed to reach universal coverage and identify if additional LLINs are required after the Global Fund LLIN distribution of March. LLIN integrity will be assessed during the baseline year (where already used) and at the end of the study period using WHO recommended assessment of durability. The association between integrity and protectiveness will be analysed.

### **3.7. Monitoring of interventions including sociological data**

Cross-sectional surveys using questionnaire will assess user acceptability and perception of sustained IRS and LLINs. Questions asked will be to determine specifically what the villagers like and dislike about the interventions, whether they experienced any symptoms from the presence of insecticide, whether they have perceived any benefits from LLINs/IRS. IRS coverage is purportedly very high in the district at 96.7% which appears to indicate a high level of co-operation and user acceptance. Questionnaires will address specific issues of user fatigue after several spray rounds of IRS and perceived negative associations such as increase in other pests (an increase in fleas has been reported in some households).

Complementary to questionnaires, focus group discussions (FGD) with male and female household members from each arm of the trial will be carried out in collaboration with anthropologist/sociologist from NIMR Mwanza to assess initial responses to IRS, potential benefits and drawbacks compared to

current methods of protection (LLINs), and the reasons for non-compliance. A further round of focus group discussions during the intervention stage will consider perceptions of efficacy and persistence.

### **3.8. Data collection and analysis**

Household questionnaires for the baseline and interventions cross sectional surveys will be programmed into PDAs and downloaded into Microsoft Access via Pendragon forms 5.1 software. This allows continual checking of the data without the need to wait for data entry. Entomological data will also be entered using PDAs. Clinical data will be recorded on paper in the field because these forms must be passed between the nurses doing the examination and the dispensing officer (clinician), who must approve each copy. The forms will then be double entered, validated and verified by data entry clerks in the PAMVERC office.

The full analytical plan will be developed later. Given the nature of the interventions it is not possible to conduct a blinded trial. Stratified randomisation of villages to the study groups will reduce the likelihood of chance imbalances between study arms but as only relatively small number of units can be randomized in such a cluster design, the 2 groups cannot be assumed similar for all factors. Data on parasite prevalence and anaemia will be collected for sampled children during baseline to adjust for any imbalances in malaria at clusters level. Only houses in the core sampling areas, situated at least 1 km apart from the next cluster will be selected to reduce any spill-over effect (where an anti-vector intervention may also reduce or increase transmission in neighbouring villages).

Individual data will be collected on potential confounding factors to allow for adjustments in the final analysis. Potential confounders to be probed during cross sectional surveys include home treatment/prophylaxis of malaria, travel to other areas with different levels of transmission, and the use of other anti-mosquito measures which may prevent malaria transmission such as insecticidal sprays, coils, repellents, smoke, quality of LLINs by recording the number of holes and usage and quality of spraying (using pyrethroids detection kits). Household and personal data will be analysed with parasite prevalence data to identify and quantify individual, household and environmental risk factors.

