## 2.5. Data analysis

Since compliance with LLIN or LLIN plus IRS allocation may not be fully adhered to, both intention to treat and per protocol analysis will be performed. To do this, household ownership and usage of LLINs and whether the house was sprayed will be determined for each individual whose infection status is measured, in each survey. Data analysis will be based on methods that make allowance for between-cluster variation (intra-cluster correlation) of responses. Data analysis will be carried out using both cluster level approaches and individual level regression approaches using random effects models. Point estimates and confidence intervals of rate ratios of malaria episodes (odds ratios of infection prevalence and anaemia) in intervention arms, relative to the reference arm, will in the first instance be based on cluster summaries. Poisson regression will be used to estimate intervention effects on malaria incidence rates and logistic regression models will be used to estimate intervention effects on prevalence of infection and prevalence of anaemia, adjusted for individual and cluster specific confounders, using random effects models.

By including vector species (*Anopheles gambiae* s.s., *An.arabiensis* and *An.funestus*) as a cluster level co-variate, it may be possible to investigate the effect of vector species on vector control effectiveness.

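### Section 3.8 lists spray quality and net use as confounders for adjustment; measured after allocation they are delivery or possible effects of the intervention, and adjusting for spraying may favour a false finding of non-inferiority

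*Protocol*

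**What the plan says.** Section 3.8 states that "Individual data will be collected on potential confounding factors to allow for adjustments in the final analysis". Its list of potential confounders, to be asked about in the cross-sectional surveys, includes home treatment or prophylaxis, travel, other anti-mosquito measures, and "quality of LLINs by recording the number of holes and usage and quality of spraying (using pyrethroids detection kits").

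Section 2.5 says that the Poisson and logistic models estimating intervention effects are "adjusted for individual and cluster specific confounders, using random effects models". It also says that point estimates and confidence intervals "will in the first instance be based on cluster summaries", and that "both intention to treat and per protocol analysis will be performed". Section 3.8 adds: "The full analytical plan will be developed later".

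Four other places bear on the timing and nature of these variables:

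- Sections 2.2 and 3.6: the randomised contrast is the IRS round of September-October 2011, given in one arm only.
- Section 2.3: net usage and perception under reduced IRS is secondary outcome 8.
- Section 3.5.3 and the Stage IV work plan: pyrethroid kits are used in the intervention year, and both post-intervention surveys record evidence of the September 2011 spraying.
- Stage III work plan: the kit is also used at baseline, in May-June 2011.

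**The concern.** A confounder is a common cause of allocation and outcome. After the September-October 2011 round, whether and how well a house was sprayed is the treatment itself, as delivered. Net use, net holes and coils or repellents are not the treatment, but they may change once spraying stops, and the protocol treats net use as something to be measured for that reason. Conditioning on such variables changes the question from the total effect of withdrawing IRS to the part of that effect left after the conditioned pathway is removed.

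This matters more than usual because the trial asks about non-inferiority. If part of the benefit of IRS is credited to the spray variable, the arm coefficient moves towards no difference, which is the direction that supports withdrawal. Section 2.2 says the result is meant to give assurance that withdrawal is safe. A later analytical plan would not merely fill a gap here: it would start from a list that already misclassifies these variables.

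**Working it through.** **1. Reproduce the plan's own figures.** Table 1 follows from

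c = 1 + (z_α + z_β)² × [(p0(1−p0) + p1(1−p1))/m + k²(p0² + p1²)] / d²

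with m = 100 and 80% power. The superiority column uses two-sided 5% and p1 = p0 − d. The non-inferiority column uses one-sided 5% and p1 = p0. All 14 rows match in both columns. For the last row (4%, margin 3 points, k = 0.6), (1.645 + 0.842)² = 6.18, and the bracket is 0.000768 + 0.001152 = 0.00192. Then 1 + 6.18 × 0.00192/0.0009 = 14.19, so 15, as printed. One-sided 2.5% would give 18. The check below therefore uses one-sided 5%: non-inferior if the upper limit of the 90% interval lies below the margin.

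**2. Inputs.** From the protocol: 15 clusters per arm (2.3), 100 children per cluster, prevalences, margins and k (2.6, Table 1), and 96.7% spray coverage (3.7). Assumed: the share f of the IRS effect acting through the child's own house (0, 0.5 or 1, the rest community-wide); kit-positive shares of 80% and 60% as alternatives to 96.7%; no spraying in arm B.

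Margins as odds ratios: (0.15/0.85)/(0.10/0.90) = 1.59 and (0.07/0.93)/(0.04/0.96) = 1.81.

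**3. Why the adjusted model is fragile.** With no sprayed houses in arm B, the adjusted arm coefficient rests on comparing arm B with unsprayed children in arm A. At 96.7% coverage these number about 15 × 100 × 0.033 = 50. For coverage c in arm A and none in arm B, the squared correlation of arm with spray status is c/(2−c) = 0.967/1.033 = 0.936. The variance inflation, ignoring clustering, is 1/(1−0.936), about 15.7.

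**4. False non-inferiority, true difference at the margin.** 2,000 simulated trials per scenario, logistic regression with cluster-robust standard errors as a stand-in for the planned random-effects model. Simulation error is at most about 1.1 percentage points, from √(0.25/2000). Without adjustment the rate is 4-7% throughout. Adjusted for household spray status:

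| Scenario | Coverage, arm A | f = 0 | f = 0.5 | f = 1 |
|---|---|---|---|---|
| 15% v 10%, k = 0.3 | 96.7% | 5% | 12% | 29% |
| | 80% | 5% | 24% | 67% |
| | 60% | 5% | 21% | 80% |
| 7% v 4%, k = 0.6 | 96.7% | 5% | 12% | 24% |
| | 80% | 5% | 19% | 55% |
| | 60% | 6% | 18% | 62% |

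In the first scenario the true odds ratio of 1.59 becomes 1.59-1.66 at f = 0, 1.28-1.35 at f = 0.5 and 1.00 at f = 1.

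**5. Power, arms truly equal.** At 10% and k = 0.3, power is 83-85% unadjusted. Adjusted, it is 22% at 96.7% coverage, 58% at 80% and 72% at 60%. At 4% and k = 0.6, it is 62-64% unadjusted and 20%, 43% and 52% adjusted. These tests are on the odds-ratio scale, so they are not directly comparable with the 80% behind Table 1, which is on the absolute scale. Model fits that failed at 96.7% were counted as not non-inferior, so the adjusted figures at that coverage are, if anything, low.

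**6. Net use.** Assume a net odds ratio of 0.5 and 60% use in arm A. In each arm, solve n × expit(b + ln 0.5) + (1−n) × expit(b) = p, with p = 10% in arm A and 15% in arm B. The net-adjusted arm odds ratio is exp(b_B − b_A), against a total of 1.59:

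| Net use, arm B | Adjusted odds ratio |
|---|---|
| 80% | 1.86 |
| 70% | 1.72 |
| 50% | 1.49 |
| 40% | 1.39 |

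More net use in arm B moves the estimate away from non-inferiority; less moves it towards non-inferiority.

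**The case against.** The protocol does not fix a covariate list for the arm-effect model. The factors are only potential confounders, collected so that adjustment is possible; the full plan is to follow; and cluster summaries, for which no such adjustment is stated, come first. A reader might infer that the final analysis is bound to adjust for spraying. The text does not go that far, and the first-line estimate is not shown to be affected. What remains is that section 3.8 puts these variables under the wrong label and section 2.5 adjusts planned estimates of the intervention effect for whatever carries that label.

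The surveys include the baseline one, and the kit is used then too, so the listed variables could be read as baseline values. But the protocol also measures spraying after the September-October 2011 round, and nothing restricts adjustment to the earlier values.

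Sections 2.5 and 3.8 already foresee sound uses for the data: per protocol and risk-factor analyses. That is true, and the fix keeps them.

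A reader might also extend the point to vector species, which section 2.5 would enter "as a cluster level co-variate, it may be possible to investigate the effect of vector species on vector control effectiveness", because section 3.5.2 says "The relative composition and abundance of these species is likely to have changed significantly as a result of IRS". The documents do not support this. The wording is exploratory, the change described dates from the start of IRS in 2007, before randomisation, and species are measured in the pilot.

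**Conclusion.** The point holds in a limited form. Post-allocation spray status is delivery of the randomised intervention, and post-allocation net use may be a consequence of it. Listing them as confounders for adjustment of the arm effect is wrong as written.

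For spray status the possible bias is towards a false non-inferior result. At the 15% v 10% margin the error rate goes from about 5% to 12-24% if half of the IRS effect is household-level and 29-80% if all of it is, with no inflation if the effect is wholly community-wide. That share is an assumption; the protocol's buffer zones and its concern about spill-over suggest some area-wide component. It would therefore be too strong to say that the effect of withdrawal is adjusted away: only the household-level part is exposed. At 96.7% coverage the loss of power is at least as serious.

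Nor do all the listed variables push one way, since net-use adjustment can go in either direction. The remedy is cheap and the first-line cluster analysis is not implicated, so this is a should-fix.

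**What to change.** In sections 2.5 and 3.8, state that the intention-to-treat arm comparison is adjusted only for:

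- pre-allocation variables: pilot and baseline cluster prevalence, the randomisation strata, and other baseline characteristics as cluster-level summaries;
- individual characteristics that the intervention cannot change, such as age and sex.

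Cluster-level summaries are needed because section 3.3.1 reads as a random selection of houses at each survey, so individual baseline values may not exist for children surveyed later.

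State also that spray, net and other anti-mosquito variables measured after allocation are used only to describe delivery, in the per protocol analysis and in the risk-factor analyses.

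The cost is a few sentences. No additional data collection, clusters or surveys are needed.

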### **3.9. Ethical considerations**

Local ethical approval from KCMC has been granted (summarize comments from reviewers). Mandatory ethical clearance will be obtained from the Ethics Committees of KCMC, the National Institute of Medical Research and prior to initiating the study as indicated in the activity schedule. LSHTM ethics approval has been granted (number 5814).

Written informed consent will be obtained from the head of household or caregiver of each selected household. Community consent will be obtained from hamlet leaders.

### **3.10. Environmental Compliance standards**

PMI will be responsible for the IRS programme including safe disposal of chemicals and deteriorated LLINs. We strive to conduct all research to international environmental standards. The project does

not involve the use of large quantities of disposable waste products. The clinical samples of blood, gloves, slides, and drug packaging will be disposed of according to standard protocols.

#### 4. Work Plan

The trial will run for 2 years as per the detailed work plan and schedule. A comprehensive work plan and project schedule is outlined in this section (and is divided in 4 stages).

1. Stage 1: **The preparation** (Sept-Dec 2010) during which the project was established in Kagera region. A project manager ([name]) was recruited and based in Muleba. A project office was secured in Muleba as a headquarters for field activities, administration, reference laboratory and entomology. Project staff were recruited and trained. Coordination with district health authorities was achieved.

The main technical activity during the first quarter was the mapping of the trial area consisting of more than 100 villages in which the study will be conducted. Each house in each hamlet was geo-referenced to facilitate the allocation of interventions and the sampling of households for cross sectional surveys and entomological surveillance. A detailed quarterly report covering this phase has been submitted.

2. Stage 2: **The pilot** (Jan to March 2011). Following the mapping conducted during the preparatory phases, 51 clusters comprising of 1 up to 3 villages were identified, and 100 houses randomly selected per cluster. A pilot cross sectional parasite survey to evaluate prevalence in the study area is ongoing and started in February. Based on the prevalence data the final selection of study clusters will be made. An IRS round just finished before the beginning of the pilot cross sectional survey.
3. Stage 3: **The baseline** (April-Sept 2011). During this stage it is anticipate that a distribution campaign of LLINs will occur beginning April with the objective to reach universal coverage. A second cross sectional prevalence survey (June-July), entomological monitoring, a feasibility evaluation of acquiring incidence data from health facility integration will be also conducted. The laboratory will be fully set up, SOPs for the different techniques written and staff trained.
4. Stage 4: **The intervention**, (Sept 2011-Aug 2012) anticipates IRS in Sept-Oct 2011 in half the clusters and distribution of LLIN to top up the universal campaign and reach a coverage and usage of minimum 80% in all the cluster. It will depend on whether RTI is sprayed in Sept 2011 or February 2012. Cross sectional prevalence surveys in Feb-March and again in June-July, with entomological and incidence monitoring from Jan-July will also be conducted.

| Activity                                               | Tool                                                                                                           | Outcome measures                                                                                                                                                                                                                                                                                                                                                                                                                                                                                                                                   | Target deadline                                                                                                                                                                                                                                                                                                                                                                                 |
|--------------------------------------------------------|----------------------------------------------------------------------------------------------------------------|----------------------------------------------------------------------------------------------------------------------------------------------------------------------------------------------------------------------------------------------------------------------------------------------------------------------------------------------------------------------------------------------------------------------------------------------------------------------------------------------------------------------------------------------------|-------------------------------------------------------------------------------------------------------------------------------------------------------------------------------------------------------------------------------------------------------------------------------------------------------------------------------------------------------------------------------------------------|
| Stage I – Preparation (September-December 2010) |                                                                                                                |                                                                                                                                                                                                                                                                                                                                                                                                                                                                                                                                                    |                                                                                                                                                                                                                                                                                                                                                                                                 |
| Staff recruitment                                      | Advertisements (already distributed)
Interviews (already scheduled)
Appointments made & contracts signed | Following staff in place: Position (contracted to/based at)

 
1. Trial manager (LSHTM/Muleba)
 
2. 8 Field Technicians (KCMC/Muleba)
 
3. Trial administrator (KCMC/Muleba)
 
4. Trial accountant (KCMC/Moshi)
 
5. Driver (KCMC/Muleba)
 
6. 2 security guards (KCMC/Muleba)
 
7. Data entry clerk (KCMC/Muleba)
 
8. 2 Laboratory technicians (KCMC/NIMR)
 
9. 4 Nurses and 2 clinical officers (temporary appointment/Muleba)
 
 | 
 
1. Achieved Q1.2
 
2. 7 employed Q1.1-1.2
 
3. Achieved Q1.1
 
4. Achieved Q1.1
 
5. Achieved Q1.1
 
6. Achieved Q1.1
 
7. To be identified in Q2
 
8. Identified in Q1.1
 
9. To be done in Q2 before survey
 
 
PhD student involved on the epidemiological part of the study Q2
 |
| Ordering equipment                                     | Administrator LSHTM
Administrator KCMC
(invoices, proforma etc)                                          | Purchase of major laboratory equipment: 
 
1. RT-PCR machine
 
2. 3x Laptop computers
 
3. 2x Microscopes
 
4. 20/20 Stand-alone reader
 
 Purchase of major field equipment: 
 
1. 5x GPS units
 
2. 5x Motorbikes
 
3. 5x PDA units (
 
4. 50 x light traps & batteries
 
5. RDTs and ACTs
 
                                                                                         | 
 
1. Achieved Q2
 
2. 3 purchased Q2.1-1.2
 
3. Achieved Q1.2
 
4. Achieved Q1.1
 

 
1. Achieved Q1.1
 
2. Planned for Q2
 
3. Achieved Q1.2
 
4. Achieved Q1.2
 
5. To be done in Q2
 
                                                         |
| Setting up offices                                     | DMO Muleba to identify and assign an office                                                                    | 
 
• Signed 1 year renewable contract agreement with DMO to rent one office within district administration site offices
 
                                                                                                                                                                                                                                                                                                                                                                             | Achieved Q1.2                                                                                                                                                                                                                                                                                                                                                                                   |
|                                                        | Meeting with landlady of private guesthouse (already identified)                                               | 
 
• Signed 1 year renewable contract agreement to rent private guesthouse to equip for purpose of the project
 
                                                                                                                                                                                                                                                                                                                                                                                      | Achieved Q1.2                                                                                                                                                                                                                                                                                                                                                                                   |
|                                                        | Assigning functions to the guesthouse rooms                                                                    | 
 
• Office for project manager
 
• Office for project administrator
 
• Storeroom
 
• Mosquito sorting/identification room
 
                                                                                                                                                                                                                                                                                                                                                    | Achieved Q1.2                                                                                                                                                                                                                                                                                                                                                                                   |

|                                                       |                                                                        |                                                                                                                                                                                                                                                                                              |                                                                                                                         |
|-------------------------------------------------------|------------------------------------------------------------------------|----------------------------------------------------------------------------------------------------------------------------------------------------------------------------------------------------------------------------------------------------------------------------------------------|-------------------------------------------------------------------------------------------------------------------------|
|                                                       |                                                                        | 
 
• Insectary
 
• 2 bedrooms for visiting project staff not based in Muleba
 
• Data management office
 
                                                                                                                         |                                                                                                                         |
|                                                       | Buying and installing furniture                                        | 
 
• Shelving for storeroom & offices
 
• Desks and filing cabinets for offices
 
• Fridge for mosquito sorting room
 
• Humidifier for insectary room
 
• Heater and/or A/C unit for insectary room
 
          | Achieved Q1.2, with the climate condition in Muleba Humidifier and heater not necessary.                                |
| Field technician training                             | 2-day GPS mapping course                                               | 
 
• Proficiency in marking, saving, editing and deleting waypoints, using the track logger, finding waypoints & using routes, using pre-determined project waypoint and track naming system, abbreviations and symbols
 
                   | Achieved in Q1.2 with knowledge used extensively during the mapping of clusters                                         |
|                                                       | 1 week intensive motorbike proficiency course                          | 
 
• Licenses for all field technicians
 
• Certification from Muleba driving school
 
                                                                                                                                                   | Plan for Q2 before field work                                                                                           |
|                                                       | 1-day slide staining course                                            | 
 
• Slide preparation training for the 2 laboratory technicians at KCMC
 
                                                                                                                                                                      | On going in Q1.2 and will continue during Q2                                                                            |
| Information dissemination and community sensitisation | Group meeting with village leaders, hamlet leaders and household heads | 
 
• Community understanding of stage one and stage two activities; verbal agreement to participate and support project activities
 
                                                                                                            | Sensitization for mapping done in Q1.2 and additional sensitization are planned before the beginning of the pilot in Q2 |
|                                                       | Reporting to HRCD                                                      | 
 
• Quarterly technical report including Performance Monitoring Report
 
                                                                                                                                                                       | Table part of the Q1.1-Q1.2                                                                                             |
| Stakeholder coordination                              | Meeting(s) with HQ representatives PMI/RTI/NMCP/WHO                    | 
 
• Established schedule of face-to-face and/or teleconference appointments to update project partner institutes
 
• Identify representatives from each institute to attend, as well as locations and meeting structure (quorum etc.)
 
 | Individual contact has been done during the past quarter with every partner. Meeting will be held during Q2             |
| Coordination Committee                                | Discussions with Kagera-based representatives                          | 
 
• Establishing Coordination Committee
 
                                                                                                                                                                                                      | To be done in Q2                                                                                                        |
| Study area identification                             | GPS                                                                    | 
 
• Geo-location data for all village centres within 45min drive of Muleba town
 
• Map main roads within study area
 
                                                                                                                  | Identification done in Q1.2                                                                                             |

